### Sample size

2.3.

According to a previously published meta-analysis comparing iTBS and sham stimulation (Zhang et al., 2017), the expected effect size Cohen’s d for the comparison of the two groups was 0.6, and the effect size (f) for the comparison of the corresponding four groups was approximately 0.3. Using G*Power v3.1.9.2, the estimated sample size required for a 4-group design with a ratio of 1:1:1:1, given a power of 0.95 and a 2-tailed alpha error probability of 0.05, is 44 patients in total. Considering a dropout rate of 20%, at least 14 participants are needed for each group. Therefore, 56 patients will be enrolled in this study.

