**Discussion:**

The iTBS intervention in this study protocol is expected to be a potential method to promote upper limb motor recovery after stroke, and the results may provide supportive evidence for the optimal dose of iTBS intervention.

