### Outcome measures

2.6.

The Fugl-Meyer Assessment of the Upper Extremity (FMA-UE) score from baseline (T0) to end of intervention (T1) is defined as the primary outcome. The FMA-UE is a standardized scale of upper limb motor impairment ranging from 0 to a maximum of 66 points (Fugl-Meyer et al., 1975; Chen Y. F. et al., 2022). Secondary outcomes are the Wolf Motor Function Test (WMFT), Grip Strength (GS), MAS, Modified Barthel Index (MBI), and Stroke Impact Scale (SIS). The WMFT consists of 15 tasks, each of which must be completed in at least 120 s, and the performance on each task is scored on a six-point scale (0–5) (Morris et al., 2001; Wolf et al., 2001). The GS is measured with a grip dynamometer. During the measurement, the patient’s shoulder joint is abducted to 90°, the elbow joint is flexed to 90°, and the forearm is placed on the table. The patient is instructed to hold the grip dynamometer as hard as possible (Bertrand et al., 2015). The grip dynamometer automatically records the highest value. A total of 3 measurements are taken with a 1-min rest interval between each measurement. The MAS is commonly used to assess spasticity. The MAS scores for the shoulder, elbow, wrist, and fingers of the affected upper extremity will be recorded. The MBI is used to assess the patient’s ability to perform activities of daily living (ADL), including 10 items out of 100 points (Ohura et al., 2017). The SIS is one of the commonly used scales to evaluate the quality of life of stroke patients, which consists of eight items, and each item has a full score of 100 points (Mulder and Nijland, 2016), and we will take the average score of the eight items as the outcome. Each participant will undergo the following clinical assessments pre-treatment (T0), post-treatment (T1), and at the 3-weeks follow-up (T2): FMA-UE, MBI, SIS. The following clinical assessments will be performed only before and after treatment: WMFT, GS, MAS. We will also perform exploratory analyses based on the rs-fMRI data collected before and after the treatment.

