### Data analysis

2.7.

We will use SPSS version 25 for statistical analysis. Analysis of variance (continuous and ordinal data) or χ^2^ tests (categorical data) will be used to compare demographic and baseline characteristics. A mixed-design ANOVA (between-subjects factor: group; within-subjects factor: time; and time-by-group interaction) will be used to detect any significant differences in the change of outcomes. Any factor with a significant difference between the groups at the baseline will be included as a covariate in the ANOVAs. If a significant time-by-group interaction effect is found, comparisons using pairwise *t*-tests will be performed by separately comparing the changes from baseline. Bonferroni correction is applied for *post hoc* tests. Before entering the data into the ANOVAs, the Shapiro–Wilk test will be used to test whether the data are normally distributed. For non-normally distributed measures, the non-parametric Kruskal-Wallis H test is performed to compare across conditions. The level of significance is defined as *p* < 0.05 (2-tailed). For missing data, intention-to-treat (ITT) analysis is used (Matilde Sanchez and Chen, 2006).

The pre-processing of the MRI data will be in accordance with the previously described pipeline (Yeo et al., 2011). After preprocessing, regional homogeneity (ReHo), degree centrality (DC), amplitude of low frequency fluctuations (ALFF), and seed-to-voxel analyses will be performed to measure functional connectivity within motor networks. ReHo is calculated based on the Kendall’s concordance coefficient, which is used to measure the time-series synchronization between a given voxel and neighboring voxels, with higher values representing better concordance between the local voxel and the regional brain activities. In network analysis, DC is the most direct measure of node centrality. A higher degree of a node means that the node has a higher DC and the node is more important in the network. The ALFF value is related to the strength of local neural activity. It is often used to measure the BOLD signal in the frequency range of 0.01–0.1 Hz (Zang et al., 2004). Differences between conditions are considered significant if *p* < 0.05 at the voxel level. A false discovery rate (FDR) cluster corrected *p* < 0.05 is applied.

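### The 95% power claimed for 44 patients does not follow from a between-group f of 0.3 on FMA-UE change: power is about 32% in change-SD units, and 95% would need a T0-T1 correlation near 0.9

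*Protocol article*

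**What the plan says.** All references are to the protocol article.

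- **Two-group effect size (2.3 Sample size).** From a meta-analysis of iTBS against sham, "the expected effect size Cohen’s d for the comparison of the two groups was 0.6".
- **Four-group effect size (2.3).** The section then converts that value for its own design: "the effect size (f) for the comparison of the corresponding four groups was approximately 0.3".
- **Sample size (2.3).** For four equal groups, G*Power gives a number that, "given a power of 0.95 and a 2-tailed alpha error probability of 0.05, is 44 patients in total". Dropout then brings it to 56: "Considering a dropout rate of 20%, at least 14 participants are needed for each group".
- **Primary outcome (2.6 Outcome measures).** The FMA-UE "score from baseline (T0) to end of intervention (T1) is defined as the primary outcome". FMA-UE is also measured at T2, three weeks later.
- **Analysis (2.7 Data analysis).** "A mixed-design ANOVA (between-subjects factor: group; within-subjects factor: time; and time-by-group interaction) will be used". Bonferroni-corrected pairwise comparisons of change from baseline follow only if the interaction is significant.
- **Intended use (Abstract, Discussion).** "the results may provide supportive evidence for the optimal dose of iTBS intervention". Comparing the three doses is the second objective in the Introduction.

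The G*Power test, the number of measurements, the correlation and the SD that standardises d are not given.

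**The concern.** The f of 0.3 is half of d = 0.6, so it describes how far group means lie apart at one endpoint. A one-way comparison of four groups with that f needs far more than 44 patients for 95% power. The 44 therefore appears to come from a routine in which the same symbol stands for another quantity, one that makes 0.3 a much larger effect than the one cited.

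The stake is how the result will be read. A non-significant interaction in a trial described as having 95% power looks like good evidence against a dose effect. If true power for the assumed effect is nearer one third, it is weak evidence. The same omnibus test also decides whether the pairwise dose comparisons are made at all.

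**Working it through.** **Inputs from the article:** d = 0.6, f = 0.3, alpha = 0.05, k = 4 equal groups, N = 44 (56 enrolled), primary comparison T0 to T1, group-by-time interaction test. **Assumed, because not given:** number of measurements m, correlation rho between visits, sphericity 1. Powers come from the noncentral F distribution.

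**1. Reproducing 44.** In the within-between interaction routine, lambda = f² × N × m / (1 − rho), with df (k − 1)(m − 1) and (N − k)(m − 1).

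| m | rho | lambda at N = 44 | power at 44 | power at 40 |
|---|---|---|---|---|
| 3 | 0.5 | 0.09 × 44 × 3 / 0.5 = 23.76 | 0.9605 | 0.938 |
| 2 | 0.6 | 0.09 × 44 × 2 / 0.4 = 19.80 | 0.958 | 0.936 |
| 2 | 0.5 | 0.09 × 44 × 2 / 0.5 = 15.84 | 0.904 | 0.868 |

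The first two rows give 44 as the smallest multiple of four reaching 95%; the third needs 52. The dropout step is consistent: 44 / 0.8 = 55, and 11 / 0.8 = 13.75, so 14 per group and 56 in all.

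**2. What f means in that routine.** Suppose groups are equal at T0 and differ with between-group spread 0.3 afterwards.

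- Three visits, profile (0, 1, 1): the centred profile is (−2/3, 1/3, 1/3), with mean square (4/9 + 1/9 + 1/9) / 3 = 2/9. Interaction f = 0.3 × √(2/9) = 0.141.
- Two visits, profile (0, 1): the mean square is 1/4. Interaction f = 0.3 / 2 = 0.15.

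At rho = 0.5, entering these values gives lambda = 0.02 × 44 × 3 / 0.5 = 5.28 and power 32.9% (three visits), or lambda = 0.0225 × 44 × 2 / 0.5 = 3.96 and power 32.5% (two visits). Conversely, entering 0.3 directly with m = 2 and rho = 0.5 amounts to f = 0.3 × √(2 / 0.5) = 0.6 on the change score, twice the stated effect.

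**3. Power for the primary comparison.** With two visits the interaction test is a one-way ANOVA on change: lambda = N × f², df 3 and N − 4.

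- N = 44: lambda = 3.96, power 32.5%.
- N = 56: lambda = 5.04, power 41.4%.
- f = 0.3 needs N = 128 for 80% and N = 196 for 95%.
- At N = 44, 95% power needs f of about 0.66 on change.

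**4. If d is in raw-score SDs.** The variance of change is 2(1 − rho) in raw-score units, so lambda = N × 0.09 / (2(1 − rho)).

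| rho (assumed) | 0.5 | 0.6 | 0.7 | 0.8 | 0.9 |
|---|---|---|---|---|---|
| power, N = 44 | 32% | 40% | 52% | 71% | 96% |
| power, N = 56 | 41% | 51% | 64% | 83% | 99% |

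The three-visit interaction, with the effect held at T1 and T2, is close to this: 33, 41, 54, 75 and 98% at N = 44.

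**5. What 44 patients can detect.** On change, f = 0.52 gives 79.5% power and f = 0.53 gives 81.2%, so 80% needs f of about 0.53. A pairwise t-test with 11 per group at d = 0.6 in change-SD units has 27% power, or 9% at alpha 0.05/6. It reaches 80% at d of about 1.26, or 1.63 with Bonferroni for six pairs.

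**The case against.** **The 44 is a correct program output.** This stands: neither it nor the dropout step is an arithmetic slip. Nor can one say which settings were entered, since at least two combinations return 44. What can be questioned is the effect size fed in.

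**The 32% is conditional.** This also stands. It holds in change-SD units, or at correlation 0.5 in raw-score SDs. With raw-score SDs and a correlation of 0.9, the correctly converted two-visit f of 0.15 gives lambda = 0.0225 × 44 × 2 / 0.1 = 19.80, power 0.958 and again N = 44. The claim could then be right. But the section reports an f of about 0.3 and mentions neither that conversion nor such a correlation. The correlations that return 44 when 0.3 itself is entered, 0.5 and 0.6, give 32% and 40%.

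**An article need not list program settings.** Agreed, and their absence is not the complaint. The power, effect size and N are stated, and they do not fit the stated primary outcome and test without a further assumption.

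**A reader might infer that f = d/2 is a second error, being the largest f that four groups spanning 0.6 can have.** The article does not support this. It gives d for iTBS against sham, not for the top dose against sham, and notes that most stroke studies used 600 pulses. If 0.6 were the lowest dose's effect, assumed means of 0/0.6/0.7/0.8 give f = 0.31. Equal steps of 0/0.2/0.4/0.6 give f = 0.22 and 19% power at N = 44 in change-SD units. Both spacings are illustrations; the article says only that more pulses should give more improvement.

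**A reader might infer that the trial promises to identify the best dose.** It says only that results may support such a choice.

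**Conclusion.** The power statement is wrong as written and should be corrected. A between-group f of 0.3 appears to have been used where the routine expects an interaction f, which for that effect is 0.14 to 0.15. For f = 0.3 in SDs of FMA-UE change, power is about 32% with 44 patients and 41% with all 56, against the 95% claimed. On raw-score SDs, power at 44 spans 32% to 96% for correlations of 0.5 to 0.9, and 95% needs a correlation near 0.9.

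These figures assume equal groups at T0, equal variances, four equal groups and an effect of exactly f = 0.3. The attribution of 44 to the interaction routine is an inference from the match in the number, not something the article states. The conclusion does not depend on any particular spacing of the dose effects, and it does not show that the trial must be enlarged.

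**What to change.** Keep 56 patients and remove the 95% power claim from the Sample size section. Restate power for the T0-T1 four-group comparison, naming the SD in which the effect is expressed and, if that is the raw-score SD, the assumed T0-T1 correlation. For example: with 44 evaluable patients, power is about 32% for f = 0.3 in change-SD units; 80% power needs f of about 0.53, or a pairwise d of about 1.26 (1.63 with Bonferroni for six pairs). If a high correlation is the basis for 44, give it with its source and show the converted interaction f.

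Report dose differences as estimates with confidence intervals, and state that a non-significant interaction will not be taken as evidence of no dose effect. Describing the dose comparison as exploratory would fit these figures but is optional.

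The cost is a rewritten sample-size paragraph, a less favourable power figure and a more cautious line on interpretation. It needs no extra patients, visits or measurements.

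### The stated 0.95 power with 44 patients does not follow from the section's own between-group f = 0.3 for the T0–T1 primary outcome, unless 0.3 is treated as an interaction effect or the T0–T1 correlation is about 0.9

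*Protocol article*

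**What the plan says.** All inputs are in the protocol article, section 2.3 (Sample size), unless another section is named.

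- Source effect: "the expected effect size Cohen’s d for the comparison of the two groups was 0.6".
- Conversion: "the effect size (f) for the comparison of the corresponding four groups was approximately 0.3". This is d/2.
- Design: "the estimated sample size required for a 4-group design with a ratio of 1:1:1:1".
- Error rates and resulting total, as section 2.3 gives them: "given a power of 0.95 and a 2-tailed alpha error probability of 0.05, is 44 patients in total".
- Allowance for losses: "Considering a dropout rate of 20%, at least 14 participants are needed for each group".
- Enrolment target that results: "Therefore, 56 patients will be enrolled in this study".
- Primary outcome (section 2.6, Outcome measures): the FMA-UE "score from baseline (T0) to end of intervention (T1) is defined as the primary outcome". That is two visits, although the same section also schedules the FMA-UE at T2: "Each participant will undergo the following clinical assessments pre-treatment (T0), post-treatment (T1), and at the 3-weeks follow-up (T2): FMA-UE, MBI, SIS".
- Analysis (section 2.7, Data analysis): a mixed-design ANOVA with group, time and their interaction. Pairwise comparisons of change follow if the interaction is significant.

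Section 2.3 names the software but not the routine, the number of measurements, the correlation between them or the scale on which f is defined.

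**The concern.** The section presents f = 0.3 as the effect for comparing four groups. Eleven patients per group is very few to detect an effect of that size with 95% power. The natural explanation is that a between-group f was entered into a routine that expects a different quantity, the standard deviation of the group-by-time interaction effects. The two are not interchangeable, and swapping them inflates the computed power.

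The trial sets out to compare three doses and to test a dose hypothesis. Readers told that power is 0.95 will take a non-significant omnibus test as good evidence that iTBS, or its dose, makes no difference. If true power is much lower, that inference fails.

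**Working it through.** **Formulas** (noncentral F, k = 4 groups, alpha 0.05, N in total):

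- One-way comparison: λ = N f², df = 3 and N − 4.
- Group-by-time interaction over m visits with common correlation ρ and sphericity: λ = N m f² / (1 − ρ), df = 3(m − 1) and (N − 4)(m − 1). Here f is the SD of the interaction effects in units of the within-cell SD.

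**Step 1: reproduce 44.** Enter 0.3 as an interaction f. The values of m and ρ are assumptions, since the article gives neither.

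- m = 3, ρ = 0.5: λ = 44 × 3 × 0.09 / 0.5 = 23.76, df 6 and 80, power 0.961. N = 40 gives 0.938, so 44 is the smallest balanced total.
- m = 2, ρ = 0.6: λ = 44 × 2 × 0.09 / 0.4 = 19.8, df 3 and 40, power 0.958. N = 40 gives 0.936, so 44 is again the smallest balanced total.

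The dropout step also reproduces: 11 / 0.8 = 13.75, rounded up to 14 per group, and 4 × 14 = 56.

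**Step 2: convert the stated f to the primary contrast.** Suppose the groups are equal at T0 and their T1 means have SD 0.3 (in score SD units). The interaction effects are then plus and minus half of each group's T1 deviation, so the interaction f over two visits is 0.3 / 2 = 0.15. Putting this in:

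λ = N × 2 × 0.15² / (1 − ρ) = N × 0.09 / [2(1 − ρ)].

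With two visits the interaction F test is algebraically the same as a one-way ANOVA on T0–T1 change. The one-way figures are therefore figures for the planned test on the primary contrast.

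**Step 3: power for T0–T1.**

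*f = 0.3 on the change score.* The correlation drops out.

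- N = 44: λ = 44 × 0.09 = 3.96, power 0.32.
- N = 56: λ = 56 × 0.09 = 5.04, power 0.41.
- Power 0.95 needs N = 196 (192 gives 0.947, 196 gives 0.951).

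*f = 0.3 in post-score SD units.*

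| T0–T1 correlation | λ at N = 44 | Power, 44 | Power, 56 |
|---|---|---|---|
| 0.3 | 2.83 | 0.24 | 0.30 |
| 0.5 | 3.96 | 0.32 | 0.41 |
| 0.7 | 6.60 | 0.52 | 0.64 |
| 0.8 | 9.90 | 0.71 | 0.83 |
| 0.9 | 19.80 | 0.96 | 0.99 |

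With 44 patients, 0.95 is reached at a correlation of about 0.90.

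Adding T2 changes little. If the T1 difference persists to T2, the interaction f over three visits is 0.3 × √(2/9) = 0.14. At ρ = 0.5, λ = 44 × 3 × 0.02 / 0.5 = 5.28, df 6 and 80, power 0.33.

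**Step 4: keep 0.3 as the interaction f, but test T0–T1 only.** At ρ = 0.5, λ = 44 × 2 × 0.09 / 0.5 = 15.84, power 0.90. A total of 52 is needed for 0.95, and all 56 give 0.965. With 44, power reaches 0.95 from a correlation of about 0.58. At ρ = 0.5 this reading means an f on change of 0.3 × √(2 / 0.5) = 0.6, twice the value stated.

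**Step 5: detectable f on the change score.**

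| Completers | Power 0.80 | Power 0.95 |
|---|---|---|
| 44 | 0.52 | 0.66 |
| 56 | 0.46 | 0.58 |

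**The case against.** The strongest defence is that 44 does reproduce, using the type of test planned in section 2.7 and the three visits at which the FMA-UE is measured. On that reading nothing was miscalculated, and with 0.3 kept as the interaction f the two-visit shortfall is small: 0.90 against 0.95 with 44, and none with all 56. This stands as far as it goes. The problem is a mismatch between effect size and test, not a slip in arithmetic. But section 2.3 itself derives 0.3 as d/2 for comparing groups. That 44 comes out when this number is entered as an interaction effect shows how the figure may have arisen, not that the power is right.

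A second defence is that 0.32 belongs to a one-way test the article does not name. This fails, because for two visits the planned interaction test is that one-way test on change.

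A third is that the result turns on a correlation and a scale of d that are unknown, since the source meta-analysis is not at hand. This stands, and it limits what can be claimed. A reader might infer that the true power simply is 0.32, with a two-in-three chance of missing the planned effect. The documents do not support that as an unconditional statement: it holds if f is on change scores, or if the T0–T1 correlation is 0.5. A reader might also infer that 44 can come only from a three-visit calculation. It cannot be shown, because two visits at correlation 0.6 give 44 as well.

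Finally, an article may leave software settings to the full protocol. Their absence alone would be no finding. The finding is that the published N, power and effect size do not fit together for the stated primary outcome.

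**Conclusion.** The concern holds in this conditional form. Read as section 2.3 defines it, f = 0.3 gives 44 completers a power for the T0–T1 outcome anywhere from 0.24 to 0.96 over correlations of 0.3 to 0.9, and 0.32 if it applies to change. The stated 0.95 is met only at a T0–T1 correlation of about 0.9 with f on the post-score scale, or by treating 0.3 as an interaction effect with a correlation of at least about 0.58 for two visits. The article states neither condition.

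These figures assume equal groups of 11 (or 14), normal errors with common variance, no group difference at T0, and the same variance at T0 and T1 where post-score units are used. The value f = 0.3 is accepted as given, and how well d = 0.6 supports it is not examined here.

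**What to change.** Rewrite section 2.3 as follows.

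1. Withdraw the unconditional 0.95.
2. Define the calculation for the T0–T1 group-by-time test, equivalently the four-group comparison of FMA-UE change. Name the routine, the number of visits, the assumed correlation and the scale of f.
3. Report power for 44 and 56 as a range over plausible correlations, with 0.32 and 0.41 labelled as the change-score scenario.
4. Give the detectable f on change: 0.66 with 44 and 0.58 with 56 for power 0.95; 0.52 and 0.46 for power 0.80.
5. State that a non-significant omnibus test is not evidence that dose has no effect.

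Enrolment stays at 56 and no data collection changes. The only cost is a less favourable stated power.

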### Randomization and blinding

2.4.

Block randomization method will be used in this study. Once informed consent and baseline data have been obtained, all eligible participants will be randomly assigned to four groups using a random number sequence generated by SPSS 25.0 software. Random assignment is carried out by an independent researcher and kept in a sealed opaque envelope. The researchers responsible for iTBS will not be involved in the study design, recruitment, randomization, assessment, or data analysis. Participants and other researchers (such as outcome assessors or statisticians) will be blinded to the group allocation.

### Interventions

2.5.

A transcranial magnetic stimulator (Neurosoft LLC, [name]) equipped with a figure-of-eight coil (7 cm in diameter) is used to perform the iTBS procedure. An active stimulation coil is used to deliver the active stimulation, and a sham stimulation coil is used to deliver the sham stimulation. Prior to intervention, resting motor threshold (RMT) is determined by applying a single pulse of TMS over the contralateral M1 (Tscherpel et al., 2020). RMT is defined as the minimum stimulus intensity to elicit a motor evoked potential (MEP) of 50 μV in at least 5 out of 10 consecutive trials in the relaxed abductor pollicis brevis muscle. In addition, the participants will undergo magnetic resonance scans. Similar to a previous study from our group, in this study, we will first iteratively segment the cerebral cortex of each patient into 18 functional networks based on the rs-fMRI data for each patient, thereby defining the Upper Extremity Sensorimotor Network (UESN) and the confidence values for each vertex in the UESN. Considering that TMS is likely to have the strongest influence on the gyrus crown, we exclude vertices located in the sulci, and then determine the individualized stimulation target within the UESN of the ipsilateral hemisphere on the basis of the highest confidence value. Then, according to the results of the randomized assignment, each patient will receive the navigated iTBS treatment once a day for 21 consecutive days for his or her group. The iTBS paradigm of three 50 Hz pulses repeated at 5 Hz frequency will be used, with each stimulus 2 s followed by 8 s rest, for a total of 600 pulses over 200 s. The stimulation target will be verified and maintained by a frameless neuro-navigation system (Brainsight 2; Rogue Research, Montreal, QC, Canada). The stimulation intensity is determined to be 90%RMT. The iTBS treatment in the four groups is shown in Figure 2.

